**Fig. 1 Fig1:**
[figure not shown]
Trial schema and participant flow diagram for each wave. Each pair of clusters was recruited in 1:1 allocation in one wave each (four waves in total)

### Criteria for withdrawal

We define ‘withdrawal of consent’ as the participant’s voluntary termination of informed consent to participate which they can give at any point during the conduct of the study. All potentially eligible participants will be fully informed about the study procedures by the participant information leaflet which will state that participation is voluntary and they are free to withdraw at any time without giving a reason. We will retain participants’ data if they withdraw from the study, unless the participant specifically requests withdrawal of their data. All side effects will be reported to the Principal Investigator (PI). Minor side effects will not be regarded as criteria for withdrawal, such as skin irritation, sleep disturbance, and headache or nausea.

### Expressions of interest and informed consent

The LAGs will propose and contact relevant stakeholders to promote the study 12 weeks in advance of programme delivery in their selected pair of districts. Information briefing sessions will be organised by ICS in the community. Each member of the LAG will be provided with promotional material for distribution and will be asked to promote the study through their local channels. Local press releases will be issued. LAG members will be provided with leaflets and posters which will be displayed in local pharmacies, GP surgeries, shops, and dentist and community centres and disseminated outside schools. LAG members will share posts on their organisations’ social media platforms and through their statutory and community contacts. The RA will assist in the promotion of the study through information stands at community events and at local facilities, e.g. creches. The PI will contact the local primary care centres directly and use radio to promote recruitment.

Six weeks in advance of programme delivery, a live project webpage will provide information on the research study and on the districts open for recruitment. Potential participants may express interest in taking part in the study via (i) self-registration through the project website, by telephone or by email, or (ii) referral by their general practitioner, local pharmacist, public health nurse, or community worker who will complete the online registration form on their behalf.

All expressions of interests received will be screened against the inclusion and exclusion criteria. Potentially eligible participants will receive a project information pack containing the participant information leaflet and consent form. The RA will then meet with eligible participants who have had at least 24 h to consider participation to obtain full explicit written consent including consent for salivary sampling. Baseline demographic data will be obtained at time of consent. Consent of recruited women per cluster and across each cluster pair will be obtained prior to breaking the randomisation code; hence, the RA will be blinded to the allocation (Fig. 1).

### Randomisation and allocation concealment

Four matched pairs of districts (eight clusters) will be randomised with each matched pair of clusters randomised to intervention or controls in a 1:1 allocation ratio. The randomisation will follow a pragmatic approach whereby paired districts ready for the intervention will be randomised first, followed by the next available matched pair; this accounts for temporal changes and will provide a balanced design.

The randomisation will be conducted remotely by the Wellcome Trust Clinical Research Facility (CRF) independent of the Trial Management Team, who will develop a standard operating procedure for this process. The code for each matched pair of districts will be concealed and securely stored by the Wellcome CRF at St. James’s Hospital. It will be revealed to the WCQ2 trial team once sufficient numbers have been recruited (or by agreement with the Trial Management Group (TMG) if recruitment is insufficient prior to intervention delivery). Practitioners will be informed of the area in which they will deliver their programme by the research team, and participants will be informed of their allocation by the practitioners. Figure 1 displays an overview of cluster randomisation process.

#### WCQ2 training

Community workers who are identified by the LAG as being interested in delivering the WCQ2 intervention will be trained as facilitators. These potential facilitators may be ex-smokers themselves. The WCQ training programme incorporates the findings of the original WCQ development study [15] and the National Practice Standard in Smoking Cessation [9]. It is a 3-day training programme, co-designed and delivered by HSE specialist trainers and Irish Cancer Society officers. The content includes brief intervention and motivational interviewing techniques in smoking cessation. On successful completion, new CFs are provided with a Community Facilitators Resource Pack [22] containing recommended session plans, resources, and monitoring and feedback tools for the 12-week programme. Within 6 months of the start of programme delivery, CFs are also required to complete an 8–10-h online accredited National Centre for Smoking Cessation Training (NCSCT) programme. Ongoing mentoring and support is provided by each of the partners, and refresher training is provided by the Irish Cancer Society on an annual basis.

All practitioners and researchers involved in our study will be trained in Good Clinical Practice Guidelines.

#### Intervention delivery

Participants randomised to the intervention will receive 12 weekly behavioural support group sessions in a community setting, e.g. resource centre, and NRT dispensed by the community pharmacists. The group sessions are designed to enhance positive social support systems among peers. NRT is made available without cost to all intervention participants.

Each programme will be delivered in a local community facility by two trained CFs. Each session will last approximately 90 min. The CFs will make proactive personal contact both during and between sessions with participants using their own language and cultural style, and provide an opportunity to share testimonials and personal experiences. They will promote social support with delivery of emotional support (e.g. through demonstrating empathetic listening) among peers and will also carry out regular carbon monoxide (CO) monitoring.

#### Control arm

Participants randomised to the control arm will receive a face-to-face individual smoking cessation programme offered by the HSE for men and women delivered by a Smoking Cessation Officer in a community setting [9]. This was chosen as a more suitable control intervention rather than the more readily accessible and widespread telephone and online service due to the difficulty in obtaining data on these services and similarity to the WCQ in terms of providing a face-to-face service. However, it is recognised that only a minority of women have access to this ‘Rolls Royce’ service due to lack of staff availability for service provision.

This programme encompasses, on average, 6–7 individual contacts offered in a primary care centre or hospital outpatient clinic. Sessions vary in duration and mode of delivery; however, the first of these is delivered face-to face (average session length between 30 and 45 min). Subsequent visits occur weekly or every 2 weeks and may be conducted by telephone.

Components of the behavioural support elements of the HSE programme include reinforcing motivation to quit and setting a quit date, building a repertoire of client coping strategies, providing information on the nature of tobacco addiction and withdrawal, undertaking regular carbon monoxide checks and giving feedback on progress, and planning ongoing coping mechanisms and support. Clients are informed about NRT and other smoking cessation pharmacotherapies and are advised to consult their general practitioner on these. HSE clients will obtain these free of charge if they are eligible for free General Medical Services (GMS).

#### HSE standard tobacco cessation training

HSE Smoking Cessation Officers are trained to offer behavioural support and smoking cessation advice. The intensive 2-day training they receive follows the National Standard for Tobacco Cessation Support Programme manual (2013). It includes face-to-face training and online training and assessment. Most HSE Smoking Cessation Officers have clinical backgrounds, e.g. nursing, with some psychotherapy training.

### Outcomes

#### Primary outcome

The primary study outcome is assessment of whether the recruitment target of 8 districts (clusters) and 194 women is achievable within 18 months of programme start. The recruitment rate will be estimated for each wave. It will be defined as the number of women who consent to participate (the numerator), divided by the number of eligible women who have registered with the programme.

The four matched pairs of disadvantaged geographical districts (clusters) will be based on the number of eligible women within in each matched pair of districts (approx. 16,000–20,000). Each pair will be randomised to intervention or to usual care. Subsequent recruitment of 24–25 women who consent to participate in each of the eight districts (97 in each trial arm) will occur during four 12-week periods. The percentage of eligible women needed to plan a DT will be estimated.

Eligibility rates will be established from registration details entered by either the participant or a person acting on their behalf (e.g. GP) on the WCQ2 webpage. Contact details of potential participants will be recorded at the point of expression of interest. Dropout rates will be calculated between time of confirmation of eligibility and time of consent. Number of consented women will be recorded prior to randomisation.

#### Secondary outcomes

The secondary outcomes are as follows:
(i)Retention and data completion rates in each trial arm at 12 weeks and 6 months post-quit date (set in week 2) as a follow-up time point for a future DT(ii)Proportion who are continuously absent from smoking (as per Russell’s Standard) [23], at 12 weeks (primary outcome for a future DT) and at 6 months after their quit date, corroborated by salivary cotinine and anabasine(iii)Proportion of enrolled smokers who engage with smoking cessation services in each trial arm (engagement is defined as arrival for a first face-to-face appointment with a smoking cessation adviser and having set a quit date)(iv)Number of sessions attended in each trial arm(v)Proportion in each arm who report improvement in health status measured at baseline (week 1) and 12 weeks and 6 months

Data collection will be carried out at week 1, at week 12, and at 6 months post-quit date by the RA via a detailed face-to face questionnaire. Socio-demographic characteristics, smoking behaviour, quality of life (measured by the Short Form-12, Version 2 survey [24]), and health status will be recorded at week 1. Retention and data completion rates, changes in smoking behaviour, and health status will be collected at weeks 6 and 12. Salivary cotinine ± anabasine to biochemically validate self-reported smoking cessation will be recorded at week 12 and 6/12. Attendance sheets will be provided by service delivery providers. A thank you payment (€20 shopping voucher) will be provided at 12 weeks and at 6-month follow-up to encourage continued participation.

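### Baseline smoking behaviour, SF-12 and health status are taken at programme week 1, after women learn their arm, although a consent visit before code release is available; the instrument schedule also needs reconciling

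*Protocol article*

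**What the plan says.** **Consent visit.** Under Expressions of interest and informed consent, the Research Assistant meets each eligible woman to take written consent. "Baseline demographic data will be obtained at time of consent". Consent across a cluster pair "will be obtained prior to breaking the randomisation code; hence, the RA will be blinded to the allocation".

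**Disclosure.** Under Randomisation and allocation concealment, the code for a pair is released once enough women have been recruited, or by agreement of the Trial Management Group if recruitment falls short before delivery. Practitioners are then told where they will deliver, and "participants will be informed of their allocation by the practitioners".

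**Baseline measures.** Under Secondary outcomes, socio-demographics, smoking behaviour, the SF-12 "and health status will be recorded at week 1". Outcome (v) is the proportion who "report improvement in health status measured at baseline (week 1) and 12 weeks and 6 months". Outcome (i) counts follow-up to "6 months post-quit date (set in week 2"), which shows that the weeks are programme weeks.

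**Follow-up measures.** The same section lists Research Assistant questionnaire visits at week 1, week 12 and 6 months after the quit date. It then itemises that retention, completion, "changes in smoking behaviour, and health status will be collected at weeks 6 and 12".

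**Analysis.** Data analysis plans between-group mean change scores with 95% confidence intervals, and questionnaire summaries at baseline, 12 weeks and 6 months. The Table 1 footnote labels baseline as a time point before programme delivery; the table body is not available.

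**The concern.** A baseline should not be open to influence from allocation. Here three self-reported measures are fixed at a point when a woman knows whether she has the women's group programme with free NRT or the individual HSE service. Her answers on smoking, quality of life and health may shift with that knowledge, and the direction cannot be predicted. The Research Assistant who administers the questionnaire face to face is stated to be blinded only by virtue of consent preceding code release; nothing is said about week 1.

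Any such shift enters outcome (v) and the change-score comparison directly. There is also a completeness question: women may be lost between consent and week 1, possibly at different rates in the two arms. Outcome (iii) itself allows for enrolled women who never arrive for a first appointment.

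Separately, the text does not let a reader say which instrument is due at which visit. That matters in a pilot whose primary objectives include the feasibility of data collection and the assessment of data quality and completion, because the procedure is likely to be carried into the definitive trial.

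**Working it through.** **1. Order of events, as written**

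| Step | Event | Section |
|---|---|---|
| 1 | Consent visit with Research Assistant; demographics taken; code unbroken | Expressions of interest and informed consent |
| 2 | Code for the pair released to the trial team | Randomisation and allocation concealment |
| 3 | Practitioners tell women their arm | Randomisation and allocation concealment |
| 4 | Week 1: smoking behaviour, SF-12, health status | Secondary outcomes |
| 5 | Week 2: quit date set | Secondary outcomes |

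Step 4 follows step 3, because week 1 belongs to an arm-specific programme. Socio-demographics appear at both step 1 and step 4.

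**2. How a shifted baseline reaches the result**

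With F the follow-up mean, B the baseline mean, and subscripts I and C for the arms:

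Difference in change = (F_I − B_I) − (F_C − B_C) = (F_I − F_C) − (B_I − B_C).

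If knowledge of arm moves the baseline difference B_I − B_C by d, the difference in change moves by −d, one for one. The documents give no basis for the size of d.

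**3. Completeness**

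The plan's own figure first: 194 women with 62% retention gives 194 × 0.62 = 120.3, which reproduces the stated 120 at 12 weeks. With the raw fraction, 194 × 83/133 = 121.1.

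Loss between consent and week 1 is not stated. Taking it as an assumption L, women with a week 1 baseline = 194 × (1 − L):

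| Assumed L | Both arms | Per arm | Without baseline, per arm |
|---|---|---|---|
| 0% | 194 | 97 | 0 |
| 5% | 184.3 | 92.2 | 4.9 |
| 10% | 174.6 | 87.3 | 9.7 |
| 20% | 155.2 | 77.6 | 19.4 |
| 38% | 120.3 | 60.1 | 36.9 |

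The last row supposes that all the predicted 12-week loss had already happened by week 1, so it is an extreme. Each row also supposes that no lost woman is reached for the questionnaire. A baseline at the consent visit can cover all 194.

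**4. Schedule side by side**

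| Source | Time points named |
|---|---|
| Visit list, Secondary outcomes | Week 1, week 12, 6 months |
| Itemised sentence: smoking behaviour, health status | Week 1, then weeks 6 and 12 |
| Itemised sentence: SF-12 | Week 1 only |
| Outcome (v): health status | Week 1, 12 weeks, 6 months |
| Data analysis: questionnaire scores | Baseline, 12 weeks, 6 months |
| Table 1 footnote | Baseline before programme delivery; 12 weeks; 6 months |

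Week 6 appears only in the itemised sentence. The itemised sentence does not name 6 months for health status or smoking behaviour, and it names no follow-up for the SF-12.

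**The case against.** The strongest case against is that little depends on these measures. The primary outcome is recruitment. Abstinence is counted from the quit date and checked by saliva test, so it needs no baseline score; nor do retention, engagement or sessions attended. The analysis is mainly descriptive, without significance testing. All of this stands and sets the severity.

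It can also be said that consent before code release already guards against selective recruitment. That is correct: week 1 timing cannot change who was recruited. The point here is about the answers given, not about who was enrolled.

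The words for week 1 might be a loose label for baseline, since the Table 1 footnote puts baseline before delivery. That is possible, but outcome (v) explicitly refers to "health status measured at baseline (week 1) and 12 weeks and 6 months" and the quit date falls in week 2, so programme week 1 is the natural reading. At the least the sections conflict.

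Measuring close to programme start has a real advantage. The registration webpage opens six weeks before delivery, so a consent-visit baseline could be some weeks old for early recruits. This is a genuine trade-off, which an optional short repeat at week 1 would meet.

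A reader might go further and infer that women who never start have no baseline, that no SF-12 change score can be formed, or that health status has no 6-month value. The document does not support these. The Research Assistant collects the questionnaire, and nothing ties it to attending a session. The visit list schedules a detailed questionnaire at week 12 and 6 months, and the Table 1 body, which may list every instrument, is not shown. The schedule problem is an inconsistency, not a proven omission.

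**Conclusion.** The point holds as a moderate issue, not a must-fix. As written, baseline smoking behaviour, SF-12 and health status are taken after women have been told their arm, while a visit before code release with the same Research Assistant is used only for demographics. Outcome (v) and the between-group change scores are exposed; the recruitment outcome and validated abstinence are not.

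The size of any influence from knowledge of arm cannot be estimated from the document. The possible loss of baselines rests on an assumed range: at 0 to 20% early loss, 194 down to about 155 women would have one. No stated figure in the protocol is wrong on this point. The conclusion assumes that week 1 means programme week 1, which outcome (v) and the timing of the quit date support.

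**What to change.** 1. Collect the full baseline questionnaire (socio-demographics, smoking behaviour, SF-12, health status) at the consent visit, before the code is revealed, for every consented woman. Define that visit as baseline in outcome (v). Daily cigarettes can be asked again at week 1 if a current value is wanted.
2. If the questionnaire has to stay at week 1, label it as post-allocation and report its completeness by arm against all consented women.
3. Align the consent section, Secondary outcomes, Table 1 and Data analysis in one instrument-by-visit list. Add 6 months for smoking behaviour and health status, and 12 weeks and 6 months for the SF-12. State whether week 6 is a collection point instead of simply removing it.

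**Cost.** No new visit, staff or sample size. The consent visit becomes longer, and early recruits will have some weeks between baseline and programme start. The third item is a change of wording only.

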### Process evaluation

The aim of the process evaluation is to test the robustness of trial design with respect to context for delivery of the intervention, implementation processes, and strategies from which to optimise trial methodology for progression to a full pragmatic RCT. It will be informed by the Medical Research Council guidance for process evaluation of complex interventions [25] and will use quantitative and qualitative methods to address the research aims. The domains for the process evaluation will be guided by the constructs of the PRECIS-2 tool for assessment of applicability of trial design [26].

The following outcomes will be assessed:
(i)Acceptability of the intervention form and content by participants and trial processes by participants and practitioners involved in service delivery(ii)Assessment of fidelity (the extent to which the intervention delivered as intended)(iii)Assessment of contextual factors affecting recruitment and retention(iv)Assessment of contextual factors including barriers and facilitators to implementation

Acceptability of measures and the experience of being part of a trial will be assessed quantitatively using the Acceptability of Intervention Measure (AIM), Intervention Appropriateness Measure (IAM), and Feasibility of Intervention Measure (FIM) with CFs [27], and qualitatively by semi-structured interviews with participants and with CFs once programme delivery is complete.

The interviews will be conducted using an interview guide. The focus will be on the experiences of those in receipt of the programme and those involved in programme delivery, and of being involved in a research trial. All women participating in the intervention will be invited for interview or will be purposefully sampled depending on numbers [28]. The sampling procedure will target specifically those women who were good attenders, a mix of quitters and continued smokers who completed the 12-week questionnaire comprehensively beforehand (information-rich cases) as a basis to explore the research questions more fully. Data collection will continue until saturation [29]; however, a minimum of 20 qualitative interviews will be conducted with participants. All CFs from each wave of programme delivery will be interviewed jointly, where possible.

Observational field notes will be completed to assist in the assessment of the validity of WCQ2 programme delivery [30]. A log of attendance and any adverse effects experienced by participants will be kept by the CF. Fidelity to training will be carried out through direct observation of training. Fidelity to intervention delivery will be determined using specifically designed checklists and diaries completed by the CFs in tandem once each session is delivered. The checklist will be based upon the delivery of session content determined by an intervention manual [22]. The diary will serve as a reflective tool for the CFs and for the research team to determine any deviations or adaptations in programme delivery. Confidentiality will be assured, as participants will be identified only by their role and will be provided with a pseudonym. Through the combination of diary and checklist, an assessment will be made of whether sessions are delivered as planned, or any adaptations made, in terms of content, frequency, duration, and coverage [31].

Reporting of the study methods will follow published standards for undertaking and reporting qualitative research (COREQ) [32].

The PRECIS-2 is a tool to assist trialists determine the impact of their design decisions on the applicability of an intervention in usual care [26]. The trial will be assessed against the nine domains of the PRECIS-2 wheel: *eligibility*, *recruitment*, *setting*, *organisation*, *flexibility (delivery)*, *flexibility (adherence)*, *follow-up*, *primary outcome*, and *primary analysis.* Each domain of the PRECIS-2 tool will be scored 1 to 5 to indicate how close to usual care the various design aspects of the trial are (5 usual care—pragmatic, and 1 ideal world—explanatory). The tool’s nine domains will be rated and scored by the trial team during and at the end of the intervention.

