### Objectives

The primary objectives of the trial are as follows:
(i)To determine the feasibility and acceptability of trial processes including randomisation of districts, recruitment, and data collection in both intervention and control arms(ii)To assess data quality and completion rates for the main outcome measures for a future definitive trial (DT) including biochemically validated abstinence from smoking (using salivary testing) at 12 weeks (end of programme) and 6 months (longer-term outcome)(iii)To estimate the sample size and design for a future DT including an estimate of the intra-cluster correlation coefficient (ICC) to account for the effect of ‘clustering’ in design and analysis

The secondary objectives of the trial are as follows:
(i)To test the robustness of trial design with respect to context for delivery of the intervention, implementation processes, and key mechanisms of impact, from which to optimise design of a full effectiveness trial(ii)To develop strategies to optimise recruitment and dissemination of findings to trial stakeholders to inform knowledge exchange and future research

The study protocol (version 3.0, 19 October 2018) has been developed in line with the Standard Protocol Items: Recommendations for Interventional Trials (SPIRIT) 2013 statement [16] (Additional file 1). Any changes to the protocol will be communicated to all investigators, submitted for ethical approval, and reflected in changes to the trial registry.

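### Acceptability of trial processes is a primary objective in both arms, but interviews and acceptability scales are planned only on the intervention side, and the purposive route would favour retained women

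*Protocol article*

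**What the plan says.** The Objectives section of the protocol article sets as primary objective (i) the "feasibility and acceptability of trial processes including randomisation of districts, recruitment, and data collection in both intervention and control arms".

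The Process evaluation section is where acceptability is to be assessed. Its outcome (i) includes acceptability of "trial processes by participants and practitioners involved in service delivery", and its outcome (iii) is "Assessment of contextual factors affecting recruitment and retention". The data sources it names are:

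- **Participant interviews.** "All women participating in the intervention will be invited for interview or will be purposefully sampled depending on numbers". Where sampling is used, it will "target specifically those women who were good attenders, a mix of quitters and continued smokers who completed the 12-week questionnaire". Interviews continue to saturation, and "a minimum of 20 qualitative interviews will be conducted with participants".
- **Practitioner interviews.** These are with CFs.
- **Acceptability, appropriateness and feasibility scales.** The list ends with the "Feasibility of Intervention Measure (FIM) with CFs", so CFs are the only stated respondents.

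Under Control arm, usual care is delivered by Smoking Cessation Officers, not CFs. Under Sample size, 12-week retention is taken as 62%, and retention in the usual care districts is an unknown that is expected to be much lower.

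**The concern.** The objective names both arms, but the direct evidence is planned from one. The control arm is also where acceptability of randomisation is most likely to be strained. Women consent before the code is broken and learn their allocation afterwards. Intervention women then get a 12-week group programme with free nicotine replacement for all. Control women get individual sessions, with free pharmacotherapy only if they are eligible for General Medical Services.

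There is a second, conditional difficulty. If the purposive route is taken, women are chosen for good attendance and a completed 12-week questionnaire and are then used to explain retention. The sample is selected on the thing to be explained. The planned mix is on quit status, not on attendance.

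The decision about a definitive trial is at stake. Under Progression criteria, a decision aid is to sort problems into trial problems and real-world problems and to say how each could be overcome. That requires reasons, especially from the arm in which most loss is expected.

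**Working it through.** **1. The plan's own figure.** Inputs from Sample size: 194 women, 97 per arm, 62% retention (83/133). Expected number at 12 weeks = 194 × 0.62 = 120.3, which reproduces the stated 120. The unrounded rate gives 194 × 83/133 = 121.1.

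**2. Who supplies which evidence.** This sets Process evaluation beside Primary outcome and Secondary outcomes.

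| Group | Interview | Acceptability scales | Behavioural counts |
|---|---|---|---|
| Intervention women, good attenders with completed questionnaire | Yes, either route | No | Yes |
| Intervention women, low attenders or non-completers | Only if all are invited | No | Yes |
| Control women | No, either route | No | Yes |
| CFs | Yes | Yes | Not applicable |
| Smoking Cessation Officers | No | No | Not applicable |

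The behavioural counts are retention, data completion, engagement and sessions attended, each by arm. Loss between eligibility and consent is also counted.

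**3. Size of the interview frame**, applying 62% to the intervention arm.

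- *All intervention women invited* (read as all 97 allocated): 97/194 = 50% of consented women, none of them controls.
- *Purposive route:* retained intervention women = 97 × 0.62 = 60.1, so the frame is at most about 60/194 = 31%. The good-attendance condition narrows it further by an amount the article does not allow one to compute.
- *Intervention women outside the purposive target:* 97 × (1 − 0.62) = 36.9, about 37 (38%).
- *All consented women outside it:* 194 − 60.1 = 133.9, about 134 (69%), made up of 97 controls and about 37 intervention women.

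**4. Direction and size of any distortion.** Attendance and questionnaire completion are themselves signs that a woman found the trial tolerable, so selecting on them plausibly makes the account more favourable. No size follows. The interviews are analysed thematically and estimate no rate, and there is no distortion if women inside and outside the frame hold the same views.

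**The case against.** Several points on the other side are sound.

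- *A reader might infer that interviews are restricted outright to good attenders.* They are not. The sentence before the targeting rule allows every intervention woman to be invited, so the exclusion of low attenders is conditional. Continued smokers are deliberately included as well.
- *A reader might infer that acceptability among controls and drop-outs goes wholly unobserved.* It does not. Retention, completion, engagement and attendance by arm are accepted behavioural indicators, and field notes, CF diaries and triangulation add context on the intervention side. These sources show how many women left; they are not control women's or leavers' own reasons.
- *A reader might infer that the answer to objective (i) is shown to be biased upward.* It is not shown. The interviews yield no estimate, and the feasibility part of the objective and the recruitment outcome are unaffected.
- *Much of the objective is shared across arms.* Districts are the randomised units, and the Local Advisory Groups consent to that. Women in both arms pass through the same recruitment and consent before allocation, so intervention women can speak to those steps. They cannot speak to being allocated to usual care and followed up there.
- *Information-rich sampling is a stated and referenced choice.* It suits a study of programme content. It does not suit a question about both arms, or about why women leave.
- *The article condenses a fuller protocol, and the interview guide is not shown.* But the article does not merely leave the frame open: it states who will be invited and who receives the scales.

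**Conclusion.** The concern holds as a gap in coverage. Followed as written, the plan obtains no interview or acceptability-scale data from control women or Smoking Cessation Officers under either sampling route, which does not fit the both-arms wording of a primary objective. If the purposive route is used, retention is explored only with retained women: about 37 of 97 intervention women lie outside the target, and the frame is at most about 60 of 194 consented women.

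The control-arm gap rests only on the stated frame. The figures of 37 and 60 assume that 62% retention applies to the intervention arm and that completing the 12-week questionnaire goes with being retained. The likely direction is too favourable an account. Its size cannot be derived from the article and may be nil.

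**What to change.** - Extend the interview frame to control-arm women.
- Replace the good-attender and completed-questionnaire target with purposive sampling that deliberately varies arm and attendance or completion, within the planned interviews (minimum 20, to saturation). Fixed quotas per cell are not needed and could conflict with the saturation rule.
- Interview Smoking Cessation Officers about trial processes. The scales can stay with CFs, since they rate an intervention that the Officers do not deliver.
- If none of this is feasible, restrict the acceptability conclusion to the intervention participants and CFs actually interviewed, and reword objective (i) to match.

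**Cost.** The minimum number of participant interviews need not rise, but there would be fewer in-depth accounts of WCQ content. Saturation may be harder to reach within each group, and low attenders and non-completers will be harder to contact. The Officer interviews are additional work. The topic guide needs new wording, and the change needs an ethics amendment and a registry update, as the Objectives section requires for any protocol change.
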